### Study rationale

Based on the systematic review by Kim et al. only one study has assessed the impact of financial incentive coupled with MI on treatment adherence of young adults [14]. The study was conducted using a single-site, non-randomised and applied pre- and post-test design which is not deemed to have high internal validity. Some of the established threats to the internal validity of quasi-experimental design such as pre- and post-test design include history threat, maturation threat, testing threat, lack of blinding, instrumentation, regression to the mean, selection bias and drop out [15].

## Methods/design

### Study objectives

The main aim of the present study is to use the rigour of a randomised controlled trial (RCT) to evaluate the impact of financial incentive and MI on adolescents’ linkage, retention and adherence to antiretroviral therapy and HIV care in Anambra State, Nigeria. A cost-effectiveness analysis alongside the cluster randomised trial will be conducted as a secondary aim to assess the cost per additional patient achieving viral suppression through the proposed intervention. In-depth interview (IDI) with all the healthcare providers in the intervention arm will be conducted at the end of the study to assess their perspective on the programme’s feasibility. The main outcome will be measured at the level of an individual adolescent. Cluster randomisation is being chosen for practical reasons and to prevent treatment group contamination.

### Trial design

The study will be a cluster randomised controlled trial. Clusters are HIV treatment hospitals in Anambra state. Hospitals (the clusters) will be matched by type of hospital (e.g. secondary or tertiary) and the paired units will be randomly assigned to the intervention or the control arm. The trial has two periods – intervention period and post-intervention period. Each of these periods will run for a 1-year duration. Further details of the trial are shown in Tables 1 and 2 and Additional file 1. Figure 1 shows the schedule of enrolment, interventions and assessments for the trial design.

**Table 1 Tab1:** The World Health Organisation (WHO) trial registration dataset

Data category	Information
Primary registry and trial identifying number	The Pan African Clinical Trials Registry: https://pactr.samrc.ac.za/ (PACTR201806003040425)
Date of registration in primary registry	2 February 2018
Source of monetary or material support	European Developing Countries Clinical Trial Partnership (EDCTP)
Primary sponsor	Nnamdi Azikiwe University
Contact for public queries	[contact]
Public title	Conditional Economic Incentive and Motivational Interviewing to Improve Adolescents’ Retention and Adherence to Antiretroviral Therapy and Care in South East Nigeria: a Cluster Randomised Trial
Scientific title	Conditional Economic Incentive and Motivational Interviewing to Improve Adolescents’ Retention and Adherence to Antiretroviral Therapy and HIV Care in South East Nigeria: a Cluster Randomised Trial
Country of recruitment	Nigeria
Health condition or problem studies	HIV
Interventions	Conditional economic incentive and motivation interviewing
Key inclusion criteria	All patients with HIV who had transitioned from pediatric stage to a young person/adult; age 10–19 years irrespective of CD4+ cell count; currently off antiretroviral therapy (ART) despite multiple attempts to restart; willing to restart therapy and sign a patient agreement
Study type	Interventional
Date of first enrolment	Yet to commence
Target sample size	240
Recruitment status	Yet to commence
Primary outcome	HIV viral load
Key secondary outcome	CD4+ count, adherence to ART (measured using pill count) and adherence to appointment with hospital

**Table 2 Tab2:** Protocol for conditional economic incentives

Started ART	VL response and attended for MI	Voucher value (USD)
Week 12	VL < 20	5.6
6 months suppressed	Sustained VL < 20	2.8
9 months suppressed	Sustained VL < 20	2.8
12 months suppressed	Sustained VL < 20	5.6
Total	VL suppression for 12 months	16.8 *ART* antiretroviral therapy, *VL* viral load

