### Trial sites selection

Twelve hospitals in Anambra State that offer HIV services will be randomly selected from all the hospitals in the state that provide HIV services. The hospitals included are registered by the National Agency for the Control of AIDS (NACA) to offer HIV services. The hospitals (the clusters) will be matched by type of hospital (e.g. secondary or tertiary) and the paired units will be randomly assigned to intervention or control.

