### Sample size

The sample size was calculated using a web-based sample size calculator of the UCSF Clinical and Translational Science Institute [17]. The sample size calculation is based on the proportion of patients with VL suppression ≤ 20 copies/mL – the main outcome measure. Based on a power of 80% and an α of 0.05 (two-sided), 63 patients per group will be needed to observe a 12% (assumed standard deviation of 24%) increase in the number of participants with VL suppression as previously reported [18]. After adjustment for the cluster design, based on the assumed intracluster correlation coefficient of 0.047 and a fixed cluster per arm of six HIV treatment hospitals, the effective sample size increased to 120 patients per arm (i.e. a total of 240 participants). Due to potential attrition that could arise as a result of severe adverse events, treatment failures or the participant simply deciding to withdraw, we added three participants per hospital increasing the number of participants in each arm to 138 (i.e. a total of 276 participants). A fixed number of six clusters or hospitals per arm (i.e. 12 hospitals in total for the trial) were informed by the fact that only 12 hospitals in Anambra State offer comprehensive HIV services including HIV-adherence counselling and antiretroviral treatment services and these 12 hospitals have appreciable HIV client load. Each of the hospitals will, therefore recruit 23 participants.

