### Randomisation

We will stratify each cluster unit (HIV treatment hospital) according to the type of clinic (secondary or tertiary). We will randomly allocate each HIV treatment hospital in each stratum into the intervention arm or the control arm. The randomisation schedule will be done using Research Randomiser, a web-based computer random-number generator [19]. The randomisation schedule will be carried out by an independent person who is not part of the research team.

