## Discussion

The findings of this proposed trial should provide evidence on the feasibility of applying conditional economic incentives combined with MI to improve retention and adherence to antiretroviral therapy of adolescents living with HIV in Nigeria and possibly in other sub-Saharan African countries.

We anticipate that enrolment of adolescents with HIV might be slow especially in HIV treatment hospitals with a low patient load. However, we included 12 HIV treatment hospitals that offer comprehensive HIV counselling and antiretroviral treatment services with good client load (including adolescents).

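### Allocation is described both as matched pairs and as unconstrained allocation within hospital type, and the 12 sites both as a random sample and as the only 12 comprehensive-service hospitals; each needs one statement

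*Protocol article*

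**What the plan says.** **Allocation.** The Protocol article, Trial design, matches hospitals by type and states that "the paired units will be randomly assigned to the intervention or the control arm". Trial sites selection repeats this: hospitals are "matched by type of hospital (e.g. secondary or tertiary) and the paired units will be randomly assigned to intervention or control". The Randomisation section makes hospital type a stratifier and continues: "We will randomly allocate each HIV treatment hospital in each stratum into the intervention arm or the control arm". It mentions neither pairs nor a constraint within a stratum. The Abstract puts six hospitals in each arm, and Sample size also fixes six clusters per arm.

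**Sites.** According to Trial sites selection, the 12 hospitals "will be randomly selected from all the hospitals in the state that provide HIV services". Sample size explains the number 12 differently: "only 12 hospitals in Anambra State offer comprehensive HIV services including HIV-adherence counselling and antiretroviral treatment services", and these also have sufficient client load. The Discussion agrees with Sample size: "we included 12 HIV treatment hospitals that offer comprehensive HIV counselling and antiretroviral treatment services with good client load".

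**Analysis.** Statistical analysis and Table 3 compare the arms with chi-square, Fisher, t or Wilcoxon tests. None uses hospital, pair or stratum. The paired tests listed are within-group comparisons.

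**The concern.** The independent person who generates the schedule could follow either description. Randomising within pairs of the same type forces an equal split within each type. Allocating each hospital within a stratum, with no further rule, does not. Hospital type is the only hospital characteristic the protocol names for balancing, so leaving its balance to chance defeats the purpose of naming it. With 12 clusters, an imbalance by type could be mistaken for a treatment effect, more so because the planned tests do not adjust for type. If the number of tertiary hospitals is odd, the 12 cannot all be paired within type, and full pairing by type could not be carried out.

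The two site rules define different populations. A random sample of all HIV-service hospitals would support inference to that wider group. The complete set of comprehensive-service hospitals supports inference to hospitals of that kind only.

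**Working it through.** **1. The plan's own sample size** (Sample size: difference 12, SD 24, two-sided 0.05, power 80%, ICC 0.047, 6 hospitals per arm).

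- Individual level: n = 2 × (1.96 + 0.842)² × (24/12)² = 62.8, so 63 per arm.
- Fixed number of clusters: m = n(1 − ρ)/(k − ρn) = 63 × 0.953/(6 − 0.047 × 63) = 19.76, so 20 per hospital and 120 per arm.
- Attrition: 20 + 3 = 23 per hospital, 138 per arm, 276 in total.

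The stated figures reproduce, and they do not depend on the allocation scheme.

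**2. Balance by type when only 6:6 is fixed.** There are C(12,6) = 924 allocations. Those that split both types equally number C(T, T/2) × C(12 − T, (12 − T)/2), where T is the number of tertiary hospitals. The protocol does not give T, so a range is shown.

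| T (assumed) | Equal splits | Share of 924 |
|---|---|---|
| 2 | 2 × 252 = 504 | 55% |
| 4 | 6 × 70 = 420 | 45% |
| 6 | 20 × 20 = 400 | 43% |

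If T is odd, neither type can be split equally; the best possible is a difference of one hospital in each type, in opposite directions, which still gives 6:6.

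**3. Whether the scheme changes power.** This matters only for an analysis of hospital means. The variance of a hospital mean is 24² × (1 + 19 × 0.047)/20 = 576 × 1.893/20 = 54.5. The standard error of the difference is √(2 × 54.5/6) = 4.263, and the noncentrality is 12/4.263 = 2.815. Power from the noncentral t, assuming that neither matching nor stratifying reduces variance:

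| Analysis | df | 20 per hospital | 23 per hospital |
|---|---|---|---|
| No type factor | 10 | 71.8% | 74.7% |
| Type as a factor | 9 | 70.8% | 73.7% |
| Six pairs | 5 | 61.9% | 64.7% |

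At 20 per hospital, the pair-level analysis matches the 9-df analysis once the within-pair correlation reaches about 0.19 (about 0.17 against an 8-df version). Above that, pairing has the advantage.

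**4. Whether pairing obliges a 5-df analysis.** A simulation randomised within arbitrary same-type pairs and then analysed hospital means with type as a factor on 9 df (4 tertiary hospitals assumed, 20 per hospital, 40,000 runs). Type I error was about 5% and power about 71%. The pair-level analysis of the same data had about 62%. If pairs share only hospital type, the loss comes from choosing a pair-level test and not from the allocation.

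**5. The site statements side by side.** If the frame is every HIV-service hospital, a random draw need not return the 12 with comprehensive services. If the frame is those 12, a draw of 12 from 12 is no selection. No reading makes both statements true.

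**The case against.** The strongest reply is that these are loose sentences with an evident meaning. The Abstract and Sample size fix six hospitals per arm. Pairs formed within type would supply the balance that the Randomisation section leaves unstated. Sample size and Discussion together show which 12 hospitals are meant. Much of this stands, and it rules out several stronger readings.

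- A reader might infer that independent allocation of each hospital could leave the arms unequal in number. The fixed 6:6 excludes that; only balance by type is open.
- A reader might infer that the contradiction costs about nine points of power. It does so only under a pair-level analysis with no gain from matching. The protocol plans no such analysis, and arbitrary pairing does not require one.
- A reader might infer that the trial could enrol hospitals without antiretroviral services. That means taking the random-selection sentence alone, against Sample size and Discussion. Nor does the article make any sampling-based inference to all providers in the state.
- A reader might conclude that pairing should simply be deleted. The matching is described with type as an example only; if it uses other features, pairing may be worth its degrees of freedom.

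What does not stand is the suggestion that nothing needs correcting. The section that governs the draw omits the constraint that other sections imply, and the site statements conflict on any reading.

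**Conclusion.** The point holds as an inconsistency worth correcting before the draw. Two things are not fixed: balance by hospital type, and the population the 12 hospitals represent. Under the Randomisation section with only the 6:6 total enforced, an equal split of both types would occur in 43% to 55% of allocations, assuming 2, 4 or 6 tertiary hospitals. The sample size of 63, 120 and 138 per arm is not in question. The power contrast, about 71% on 9 df against 62% on 5 df at 20 per hospital, is conditional: it assumes a pair-level analysis and a within-pair correlation below about 0.17 to 0.19. It is a reason to settle the scheme and its analysis together, not a loss already incurred. The drop from the planned 80% to about 71% reflects the small number of clusters and is not due to this inconsistency.

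**What to change.** 1. Give one scheme in Trial design, Trial sites selection and Randomisation, and state how many hospitals are secondary and tertiary. Suggested wording: *The allocation is drawn at random from all 6:6 allocations that divide each hospital type equally between arms, or to within one hospital if the number of that type is odd.* If matching uses more than type, keep pairs instead, name the matching variables and describe the draw within pairs in Randomisation too.
2. In Statistical analysis, use an analysis that respects the clusters and includes hospital type as a factor, since the present tests use neither strata nor pairs. If pairs are kept, say how the analysis handles them.
3. Replace the random-selection sentence with: *All 12 hospitals in the state that offer comprehensive HIV services are included.* Limit inference to hospitals of that kind.

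The cost is wording, provided it is done before randomisation; an allocation cannot be redrawn afterwards. Adjusting for type uses one degree of freedom, about one point of power (71.8% to 70.8%) if type explains nothing. The site correction gives up any claim to represent all HIV-service hospitals in the state.

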**Fig. 1 Fig1:**
[figure not shown]
Schedule of enrolment, interventions and assessments. *CEI – Conditional economic Incentives, MI – Motivational interviewing

### Trial sites selection

Twelve hospitals in Anambra State that offer HIV services will be randomly selected from all the hospitals in the state that provide HIV services. The hospitals included are registered by the National Agency for the Control of AIDS (NACA) to offer HIV services. The hospitals (the clusters) will be matched by type of hospital (e.g. secondary or tertiary) and the paired units will be randomly assigned to intervention or control.

### Participants

Eligibility criteria for participants will include the following: all patients with HIV who had transitioned from pediatric stage to a young person/adult; 10–19 years irrespective of CD4+ cell count; initiated into HIV care and antiretroviral therapy for minimum of 6 months; currently off ART despite multiple attempts to restart; poor medication adherence (< 95% adherence rate assessed through pill count or self-report); willing to restart therapy and sign a written informed consent (see Additional file 2).

### Intervention

A structured adherence support scheme termed the ‘Incentive Scheme’ will be applied to the intervention hospitals while the control hospitals will receive usual care. The Incentive Scheme added to the usual care involves financial incentives linked to viral load (VL) combined with attendance for motivational interviewing (MI) with an adherence counsellor trained in MI techniques. (Table 2) [14]. Training on MI will be in accordance with an MI guide that covers key points for MI as well as examples and key insights to assessing patient risk, risk reduction counselling and inspiring behaviour change [16]. Participants in hospitals randomised to usual care will receive the normal care obtainable in the HIV treatment hospitals. This typically involves monthly or bi-monthly scheduled hospital visit for medical examination, prescription refill and adherence counselling, bi-yearly VL assessment, and yearly CD4^+^ count analysis.

In addition to the usual care, participants in the intervention hospitals will receive MI at baseline and following initiation of ART, they will receive a gift voucher of US$5.6 when VL < 20 copies/mL at 12 weeks, a gift voucher of US$2.8 if the VL remains suppressed for the next 3 months, and the next 6 months, and finally a gift voucher of US$5.6 if the VL remains < 50 copies/mL at 1 year. All incentives will be conditional not only on patients meeting their VL target but attending for MI. Those with VL higher than the thresholds will not receive the incentive. The potential maximum cumulative financial incentive is US$16.8 if viral suppression is sustained for 12 months. The patient will have the liberty to withdraw from the scheme at any time point. Routine hospital data will be collected and outcomes will be assessed by changes in HIV VL and CD4+ count from baseline, at 12 months from enrolment and at 24 months to establish whether any benefit is seen from the intervention could be sustained when financial incentives cease. Each patient in the study will be assigned to a study nurse working in the HIV treatment hospital and they will be tracked with their mobile phone numbers.

### Outcomes

The primary outcome for the trial will be the difference between groups in the proportion with HIV VL suppression (≤ 20 copies/mL) by 12 months and 24 months. The secondary outcome measure will include the average change in CD4+ count, adherence to ART (measured using pill count) and adherence to an appointment with the hospital for individual participants. Viral load analysis will be done using the COBAS TaqMan 96 and the Amplilink software.

### Laboratory methods

Ten millilitres of whole blood will be collected from each patient into a Vacutainer EDTA-plasma specimen from patients who were confirmed to be HIV-1 seropositive and receiving ART. These EDTA-plasma samples will be submitted to the virology laboratory of Nnamdi Azikiwe University Teaching Hospital for routine HIV-1 VL testing by the CAP/CTM v2.0 (Switzerland, 2016). EDTA-blood tubes will be centrifuged at 1450 *g* for 25 min prior to the plasma being separated into two aliquots in 2-mL cryovials and stored at − 88 °C in an ultralow freezer until the time of testing.

The VLs of these samples will be measured using the Roche COBAS AmpliPrep/COBAS TaqMan (CAP/CTM) commercial kits according to the manufacturer’s instructions. The plasma HIV-1 ribonucleic acid (RNA) levels will be determined as copies/mL.

Viral RNA will be extracted automatically and transferred to the COBAS TaqMan system for amplification and detection. The CAP/CTM v2.0 will be implemented along with the COBAS AmpliPrep automated nucleic acid extractor and TaqMan 96 analyser. The quantification range of the CAP/CTM v2.0 is from 20 copies/mL to 10^7^ copies/mL. Each run will consist of tested samples and one high-positive control, one low-positive control, and one negative control from the kits. Results will be validated only when the three controls (NC, LPC and HPC) have passed per run. The CD4+ count analysis will be performed using the CD4+ easy count kit and the Partec CyFlow (Görlitz, Germany, 2014) in accordance with the manufacturer’s instructions.

### Sample size

The sample size was calculated using a web-based sample size calculator of the UCSF Clinical and Translational Science Institute [17]. The sample size calculation is based on the proportion of patients with VL suppression ≤ 20 copies/mL – the main outcome measure. Based on a power of 80% and an α of 0.05 (two-sided), 63 patients per group will be needed to observe a 12% (assumed standard deviation of 24%) increase in the number of participants with VL suppression as previously reported [18]. After adjustment for the cluster design, based on the assumed intracluster correlation coefficient of 0.047 and a fixed cluster per arm of six HIV treatment hospitals, the effective sample size increased to 120 patients per arm (i.e. a total of 240 participants). Due to potential attrition that could arise as a result of severe adverse events, treatment failures or the participant simply deciding to withdraw, we added three participants per hospital increasing the number of participants in each arm to 138 (i.e. a total of 276 participants). A fixed number of six clusters or hospitals per arm (i.e. 12 hospitals in total for the trial) were informed by the fact that only 12 hospitals in Anambra State offer comprehensive HIV services including HIV-adherence counselling and antiretroviral treatment services and these 12 hospitals have appreciable HIV client load. Each of the hospitals will, therefore recruit 23 participants.

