### Statistical analysis

Statistical analysis will be conducted using IBM SPSS for Windows, Version 20 (IBM Corp, Armonk, NY, USA). As shown in Table 3, descriptive statistics will be used to evaluate differences in demographic and clinical characteristics. Categorical variables will be expressed as frequencies or percentages and quantitative variables as means and standard deviations or medians and interquartile ranges. An intention-to-treat analysis will be conducted. A secondary per-protocol analysis will also be conducted. The latter will include only those participants who completed the treatment protocol originally allocated, providing results on the efficacy of the trial. If there is a significant difference between the intention-to-treat analysis and the per-protocol analysis, then the former will be reported. Comparison of dichotomous measurements between the intervention group and the control group will be conducted using the chi-square test (or Fisher’s exact test) while comparison of the mean of continuous measurements between the intervention group and the control group will be conducted using an independent *t* test. A two-sided *p* value of 0.05 will be used to indicate statistical significance.

**Table 3 Tab3:** Data analysis outline

Study objective	Outcome variable	Type of analysis
Objective 1: effectiveness of intervention	Primary outcome	
	HIV viral load	*χ*^2^ test or Fisher’s exact test
	Secondary outcomes	
	CD4+ count	Within group: paired-sample *t* tests or Wilcoxon signed-rank tests; between group – Student’s *t* test or Wilcoxon signed-rank tests
	Adherence to antiretroviral therapy (ART)	*χ*^2^ test or Fisher’s exact test
	Adherence to hospital appointment	Within group: paired-sample *t* tests or Wilcoxon signed-rank tests; between group – Student’s *t* test or Wilcoxon signed-rank tests
Objective 2: cost-effectiveness analysis	Cost-effectiveness of intervention	Incremental cost-effectiveness ratio
Objective 3: qualitative assessment of implementer’s perspective	Programme implementer’s perspective	In-depth interview (thematic content analysis)

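### The sample size treats viral suppression, a yes/no outcome, as a continuous variable with SD 24%; the stated 80% power is about 23–34% at control rates of 20–60%

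*Protocol article*

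**What the plan says.** The Sample size section declares the basis of the calculation: "The sample size calculation is based on the proportion of patients with VL suppression" at or below 20 copies/mL. With 80% power and a two-sided α of 0.05, it then says that "63 patients per group will be needed to observe a 12% (assumed standard deviation of 24%) increase in the number of participants" with suppression, citing an earlier report for the effect. No suppression rate is given for either arm.

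The cluster adjustment is "based on the assumed intracluster correlation coefficient of 0.047 and a fixed cluster per arm of six HIV treatment hospitals", after which "the effective sample size increased to 120 patients per arm", or 240 in total. Three more participants per hospital for attrition bring this to 138 per arm and 276 in total (23 per hospital). Table 1 gives the target sample size as 240.

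Two other sections confirm that the outcome is binary. Outcomes defines the primary outcome as "the difference between groups in the proportion with HIV VL suppression", and Statistical analysis says "Comparison of dichotomous measurements between the intervention group and the control group will be conducted using the chi-square test (or Fisher’s exact test"). Table 3 assigns the same tests to viral load.

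**The concern.** A calculation for a proportion needs two proportions. This one has a difference and a standard deviation, which are the inputs for comparing two means. For a yes/no outcome the SD follows from the proportion itself and lies between 0.40 and 0.50 for any p from 20% to 80%. Entering 0.24 understates the variance by a factor of roughly three to four and the required sample size by about the same factor.

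The trial is presented as having 80% power for a 12-point gain. If the real power is about a third or less, a true gain of that size would usually be missed, and a non-significant result would be read as showing that the incentive scheme does not work.

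**Working it through.** **Inputs from the protocol (Sample size):** two-sided α 0.05, power 80%, difference 12%, SD 24%, ICC 0.047, 6 hospitals per arm, 20 per hospital after cluster adjustment, 23 with attrition. **Assumed:** control suppression of 20–60%, because none is stated; 12% read as an absolute difference.

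**1. Reproducing the plan's figures.** Two means: n = 2 × (1.96 + 0.8416)² × (24/12)² = 2 × 7.849 × 4 = 62.8, so 63 per group. Cluster step with 6 hospitals fixed: m = 63 × 0.953 / (6 − 63 × 0.047) = 60.04/3.039 = 19.76, so 20 per hospital and 120 per arm. Both stated figures come out exactly. The chain is consistent after its first step, and the first step uses the wrong formula.

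**2. When would SD 24% hold?** √(p(1−p)) = 0.24 gives p = 6.1% or 93.9%. With the two-proportions formula, n = 7.849 × (p1q1 + p2q2)/0.12², a 12-point difference needs about 63 per arm only if the control rate is about 0.5% (n = 62.3) or the intervention rate about 99.5%.

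**3. Size and power with the binomial variance.** For power, the variance of the difference is (p1q1 + p2q2) × (0.047 + 0.953/20)/6, with 120 analysed per arm. The t column uses a noncentral t on 10 df (12 clusters, two arms).

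| Control rate | n per arm before clustering | Power, normal | Power, t (10 df) | Detectable at 80%, normal | Detectable at 80%, t |
|---|---|---|---|---|---|
| 20% | 206 | 34% | 29% | 22 points | 25 points |
| 30% | 247 | 29% | 25% | 24 points | 26 points |
| 40% | 267 | 28% | 23% | 24 points | 27 points |
| 50% | 265 | 28% | 24% | 23 points | 26 points |
| 60% | 241 | 30% | 26% | 22 points | 24 points |

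A pooled-variance version of the same formula gives 209–272 per arm and 27–34% power (normal). If nobody is lost and all 138 per arm are analysed, power is at most 36% (normal) or 31% (t).

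**4. Can larger clusters help?** As m grows, the effective size per arm tends to 6/0.047 = 128. The requirement falls below 128 only when control is below about 8% or above about 80%. At 20–60%, even unlimited recruitment per hospital gives 49–60% power (normal).

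**5. Critical values.** Taking SD 24% at face value with 20 per hospital, the standardised difference is 2.815. Power is 80.4% with normal critical values and 71.8% with t on 10 df. This is a second, smaller overstatement.

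**The case against.** No reading of the text makes the formula right. The fair objections concern how large the error is.

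- **The 20–60% range is an assumption.** The trial enrols adolescents off treatment or poorly adherent, and the threshold is a strict 20 copies/mL, so a lower control rate is plausible. Normal power is then 39% at a control rate of 15%, 46% at 10%, 60% at 5% and 72% at 2%. This stands: below about 8% a 12-point gain is no longer more likely missed than found on the normal approximation. Power still stays under 80% at each of these rates, and also at 70% (36%), 80% (51%) and 85% (68%).
- **The lower end rests on a test the article does not name.** The 10-df figures assume an unpaired analysis that respects 12 clusters. The article plans a patient-level chi-square or Fisher test, describes matched pairs in one place and strata in another, and a paired analysis would leave only 5 df. The point is right, but the normal approximation alone gives 28–34%. The unadjusted chi-square would reject in about 48–55% of trials with a true 12-point gain, but only because its type I error would be near 15%. That is still not 80%, and it is not valid power.
- **12% could be a relative increase.** The cited source is not available to settle it. A relative reading lowers power further, to about 5–13%.
- **Table 1's 240 may simply be the figure before attrition.** That is likely. It is a labelling matter with no effect on power.

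**Conclusion.** The concern holds. The stated size reproduces only from the comparison of two means, while the outcome and its planned test are for proportions. With ICC 0.047, six hospitals per arm, 120 analysed per arm, an absolute difference of 12 points and an assumed control rate of 20–60%, power is 23–34% across the two methods, against 80% claimed. The difference detectable with 80% power is about 22–24 points (normal) or 24–27 points (t, 10 df), roughly twice the one stated. The exact figure depends on the missing control rate. The conclusion does not, short of a rate almost at the floor or ceiling, which the protocol does not assert. This must be corrected before the power statement is relied on.

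**What to change.** Keep the 12 hospitals and 276 participants; the article says only 12 hospitals are suitable, and larger clusters would not reach 80%. Redo the Sample size paragraph with two proportions, a stated and sourced control suppression rate, ICC 0.047, six clusters per arm and t critical values, and say how many per arm are assumed analysed.

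Replace the claim of 80% power for 12% with the resulting figure. For control rates of 20–60%, 120 analysed per arm and t on 10 df, that is about 23–29% power for 12 points, or 80% power for roughly 24–27 points. Say explicitly that the 12% is an absolute difference, after checking this against the cited source. Bring Table 1's target of 240 into line with 276, or label it as the number before attrition.

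The cost is one rewritten paragraph and one registry field. The stated power becomes less favourable, and no extra patients are needed.
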